## 2. Methods

### 2.1. Aims

The primary aim of the MINUTE trial is to evaluate the effects of a multifaceted nutrition intervention and a combined nutrition and exercise intervention on physical performance (SPPB score) among frail older adults.

Primary hypotheses: We hypothesize that (1) after the 3-month intervention, both the multifaceted nutrition intervention group and the combined intervention group will show a greater improvement in SPPB score compared to the control group. (2) The improvements in physical performance and frailty in the intervention groups will be mediated by concurrent reductions in systemic inflammation and beneficial alterations in the gut microbiota composition.

Secondary hypotheses: We further hypothesize that the multifaceted nutrition and exercise combined intervention will be superior to the nutrition-only intervention in improving physical performance.

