### 4.2. Secondary Outcomes

(1) Frailty status, assessed by the change in the Frailty Index score from baseline to the 3-month, 6-month, and 12-month assessments. The change will be analyzed as a continuous variable. Changes in frailty trajectories, as measured by the Frailty Index.

(2) Changes in intrinsic capacity: the intrinsic capacity is measured using the World Health Organization’s (WHO) Integrated Care for Older People (ICOPE) approach.

(3) Malnutrition risk assessment, measured by the Malnutrition Risk Assessment Form for older adults.

(4) Frailty recovery rates, defined as the proportion of participants transitioning from a frail to a pre-frail or robust state.

(5) Cognition function is evaluated using the Mini-Mental State Examination (MMSE).

(6) Sleep condition is evaluated using the Pittsburgh Sleep Quality Index.

(7) Participant satisfaction and acceptability are evaluated using a self-administered scale.

(8) Serum protein: serum total protein, albumin, and transferrin.

(9) Urine 8-hydroxyguanosine (8-oxo-Gsn): urine oxidation marker 8-hydroxyguanosine (8-oxo-Gsn) level.

(10) Serum inflammatory factors: C-reactive protein (CRP), interleukin-6 (IL-6), tumor necrosis factor-α (TNF-α), insulin-like growth factor-1 (IGF-1), C-X-C-motif chemokine 10 (CXCL10), and chemokine C-X3-C-based ligand 1 (CX3CL1) in serum using ELISA.

(11) Changes in serum differential metabolites: using nontargeted metabolomics methods to examine the changes in serum differential metabolites in each group before and after intervention and explore the mechanism of intervention.

(12) Changes in gut microbiota: using the 16S sequencing method to detect changes in gut microbiota and differential bacterial genera among groups.

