### 4.6. Statistical Analyses

This study will employ the Intention-to-Treat (ITT) and Per-Protocol (PP) analysis sets to ensure that all randomized study subjects remain in their assigned groups. The Intention-to-Treat population will include all randomized participants, analyzed according to their assigned group. The Per-Protocol population will include only those participants who completed the intervention as prescribed and had no major protocol deviations. For missing quantitative data, the last observation carried forward method will be used. When the results of the ITT and PP analyses are consistent, the ITT results will be presented. When the results differ, the differences will be discussed. The variables will be analyzed using SPSS V.23.0 software. All statistical tests will be two-sided at the 5% level of significance. Continuous variables with a normal distribution will be shown as the mean and SD and those with an abnormal distribution will be presented as the median and IQR. Categorical variables will be expressed as a percentage or constituent ratio. Baseline characteristics will be presented for each group using descriptive statistics (means and standard deviations for normally distributed continuous data, medians and interquartile ranges for non-normally distributed data, and frequencies and percentages for categorical data). Mixed-model repeated-measures analysis of variance with adjustment for baseline characteristics will be performed for different measurement time points between groups, and interaction between groups and measurement time. For continuous outcomes, we will report the pre- and post-intervention means for the intervention and control groups, as well as the model-adjusted mean differences between groups. For binary outcomes, we will report the pre- and post-intervention percentages for the intervention and control groups, along with the adjusted odds ratios (ORs) between groups. The 95% confidence intervals (CIs) and associated *p*-values will be calculated. We will use nontargeted metabolomics methods to examine the changes in serum differential metabolites in each group before and after the intervention and explore the mechanism of intervention. We will use 16S rRNA gene sequencing to detect changes in gut microbiota and differential bacterial genera among groups. To address the second primary hypothesis regarding the potential mechanisms, correlation analyses (Spearman’s or Pearson’s correlation) and mediation analysis will be performed to examine the relationships between changes in clinical outcomes (SPPB score and frailty) and changes in biomarker levels (inflammatory markers and microbial abundance). Subgroup analyses will be conducted to investigate whether the effects of the intervention vary across different demographic and clinical subgroups.

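### Mediation is ranked as a primary hypothesis with no pre-named mediators and every test at 5%; separately, differential metabolites are defined by before/after change within each arm

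*Protocol article*

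**What the plan says.** **Rank.** Section 2.1 places this second under its primary hypotheses: "The improvements in physical performance and frailty in the intervention groups will be mediated by concurrent reductions in systemic inflammation", and by changes in gut microbiota. Section 4.6 repeats the rank: "To address the second primary hypothesis regarding the potential mechanisms". The Abstract claims less, namely that the changes run in parallel.

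**Outcomes and size.** Section 4.1 has one primary outcome, the SPPB change from baseline to three months, and Section 4.5 sizes the trial on it alone. Inflammatory factors (item 10) and gut microbiota (item 12) are secondary outcomes in Section 4.2.

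**Method.** Section 4.6 plans Spearman or Pearson correlation, and "mediation analysis will be performed to examine the relationships between changes in clinical outcomes (SPPB score and frailty) and changes in biomarker levels". The candidate mediators appear there only as classes: inflammatory markers and microbial abundance.

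**Error level.** "All statistical tests will be two-sided at the 5% level of significance".

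**Omics.** For metabolites, Section 4.6 will "examine the changes in serum differential metabolites in each group before and after the intervention and explore the mechanism of intervention"; Section 4.2, item 11, says the same. For microbiota it will "detect changes in gut microbiota and differential bacterial genera among groups".

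**The concern.** A hypothesis ranked as primary normally has a primary outcome, a fixed set of tests and a controlled error rate. This one has none of the three. Any marker or genus that crosses 5% could be reported as confirming a primary hypothesis of a randomised trial.

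Two further features weaken causal reading. The marker change and the primary outcome change appear to cover the same three months, and randomisation does not protect the path from marker to outcome. And metabolites, which are meant to shed light on mechanism, are specified by within-group change, although a randomised control group is available.

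**Working it through.** **Step 1. The plan's own figure.** The only stated size is 105 per group (Section 4.5), from n = (k−1)(z₀.₉₇₅ + z₀.₉₀)²s² / Σ(μᵢ−μ)² with k = 3, s = 2.5 and a difference of 1.4. The nutrition-only mean is not given. If 1.4 is the widest gap, the largest possible denominator is 1.3067 (means 0, 1.4, 1.4). Then n is at least 2 × 10.507 × 6.25 / 1.3067 ≈ 100.5, so 101, and 101 / 0.9 gives 113 after dropout. The figure of 105 is not reproduced, but that is a separate matter on which this point does not depend. What matters here is that every term in the formula is an SPPB quantity. Nothing is sized for mediation.

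**Step 2. False positives among the named markers.** Section 4.2 lists six inflammatory factors; Section 4.6 names two clinical outcomes, SPPB and frailty. That makes 6 × 2 = 12 tests.
- Independent tests: 1 − 0.95¹² = 46.0%.
- Correlated tests, simulated with 284 participants (315 × 0.9), marker correlations of 0 to 0.7 and outcome correlation of 0.3 or 0.6 (all assumed): 27% to 44%.
- Genera come on top, in a number the protocol does not state. As illustration, with independent tests: 24 tests give 70.8%, 50 give 92.3%, 100 give 99.4%.

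**Step 3. Timing.** Section 2.1 calls the marker reductions concurrent, Table 3 schedules microbiota only at baseline and three months, and Section 4.1 fixes the primary outcome at three months. Section 4.6 names no visit for the mediation analysis. The shared window is therefore an inference, though a sound one for the primary outcome.

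**Step 4. What a change-on-change association can carry.** Simulated with 95 per arm (105 × 0.9), an SPPB effect of 1.4 / 2.5 = 0.56 SD in both active arms, and no effect of the marker on SPPB. The marker shift in the active arms and the residual correlation are assumptions.

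| Marker shift (SD) | Residual correlation | Pooled correlation significant | Marker–SPPB path, adjusted for arm | Joint mediation test |
|---|---|---|---|---|
| 0 | 0 | 5% | 5% | 0.2% |
| 0.3 | 0 | 10% | 5% | 4% |
| 0.5 | 0 | 17% | 6% | 6% |
| 0.3 | 0.2 | 97% | 92% | 61% |
| 0.5 | 0.2 | 99% | 92% | 91% |

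Adjusting for arm removes the association created by group membership. It does not remove a shared cause of marker change and SPPB change.

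**Step 5. Within-arm metabolite change.** Suppose all three arms drift by the same 0.3 SD of change. In a given arm of 95, the chance of significance is Φ(0.3√95 − 1.96) = Φ(0.96) = 83%. For 0.2 SD it is 50%. The same drift cancels in a comparison with control.

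**The case against.** **Left to the analysis plan.** Feature thresholds and false discovery rules are often set in an SAP or laboratory pipeline, and a general 5% sentence does not exclude a 5% false discovery rate. This stands as far as mere absence goes. It does not settle the rank, which the protocol itself states twice against its own list of outcomes.

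**Between-group comparison is already planned.** Section 4 says outcomes are compared within and between groups, and Section 4.6 plans group-by-time models. So the metabolite wording may not exclude a contrast with control. But the metabolite-specific rule, given twice, is before/after in each group, and a general sentence does not replace it. For genera the objection holds fully: they are already compared among groups.

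**Artefacts are limited.** Samples are frozen for batch analysis, and participants are selected on the FRAIL scale, not on metabolite levels. Batch effects and regression to the mean are therefore weaker worries. Other drift common to all arms is not excluded.

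**Mediation analysis normally includes arm.** True, so confounding by arm concerns the plain correlations. Without a shared cause the joint mediation test is not liberal (0.2% to 6% in Step 4).

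**Stronger readings.** A reader might infer that false mechanistic findings are almost certain. The six named markers do not show this: about 59 independent tests are needed to reach 95%, and the number of genera is unstated. A reader might also infer that false metabolite findings would count as primary results. Hypothesis (2) does not name metabolites, and no feature count is given from which to size their number.

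**Conclusion.** The point holds in two separate parts.

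1. Hypothesis (2) is called primary while its mediators are secondary outcomes, none is pre-named, the trial is sized on SPPB alone and all tests run at 5%. For the six named markers and two outcomes, the chance of at least one false positive is about 27% to 46%, and more with genera added. The lower end rests on assumed correlations; the upper end assumes independence.
2. Differential metabolites, outside hypothesis (2), are specified by within-group change, so a common drift can pass as an intervention effect. The 83% in Step 5 rests on an assumed drift of 0.3 SD.

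Error control would not make the marker-to-outcome path causal. The 61% to 91% for the joint test require both an assumed marker shift and an assumed residual correlation of 0.2, so they illustrate the risk and do not predict it. The three-month SPPB comparison between arms is not affected.

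**What to change.** 1. **Metabolites and genera.** Define differential metabolites by the difference from control at three months, adjusted for the baseline value. Declare metabolites and genera by a 5% false discovery rate within each platform.
2. **Hypothesis (2).** Relabel it as exploratory in Sections 2.1 and 4.6, or give it a closed list of mediators with error control. For six markers and two outcomes, a Bonferroni level of 0.05 / 12 = 0.0042 brings the 46.0% down to 1 − (1 − 0.0042)¹² ≈ 4.9%.
3. **Correlations.** Adjust the change-on-change correlations for arm, and state that same-visit mediator–outcome associations are not protected by randomisation.

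Mediation of SPPB or Frailty Index at 6 or 12 months may be added only as a sensitivity analysis, adjusted for three-month SPPB and without values carried forward. It asks a different question from the three-month effect, and it does not remove all confounding. Under Section 4.6, a participant lost after three months would have the three-month value carried forward as the later outcome, which restores the same-visit analysis. Section 4.3 and Table 3 also disagree on whether inflammatory factors are sampled at 12 months; this must be reconciled before any 12-month marker is used.

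**Cost.** The main changes are analysis wording and need no new data. Fewer features will be declared, and the mechanism result loses its primary label or must meet a stricter threshold.

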
## 5. Discussion

The MINUTE trial is designed to investigate the effects of multidimensional nutritional interventions on the physical performance and frailty trajectory changes in older adults with frailty, contributing to enhanced physical function and the development of tailored intervention approaches for the Chinese population. These interventions are expected to provide practical strategies for the prevention and management of frailty among older adults in China, offering effective community intervention pathways for healthy aging.

Furthermore, this study will employ metabolomics, gut microbiota analysis, and inflammatory biomarker measurement to elucidate the underlying mechanisms of frailty and the intervention’s effects. Additionally, we will monitor multiple outcome indicators, encompassing the intrinsic capacity, risk of malnutrition, and recovery rate of frailty, offering a comprehensive perspective on the health status of the elderly. This multidimensional approach establishes actionable pathways for nutritional interventions against frailty, effectively bridging the gap between theoretical guidelines and practical implementation. Moreover, this project actively engages with multiple stakeholders, offering a scalable, sustainable, and replicable comprehensive intervention strategy for healthy aging in China.

This study offers several advantages. Firstly, it features a large sample size and long-term follow-up, employing a randomized controlled trial design. Through nearly a year of follow-up, we will assess the effectiveness and sustainability of the intervention pathway. Secondly, in China, nearly 96% of the elderly reside at home or in community settings. Our community-based project offers tailored strategies specifically designed for these home-based older adults. Thirdly, this research has strong operability and popularization. This project engages multiple stakeholders, holding meetings and discussions with various interest groups, integrating diverse perspectives, aligning with the interests of organizations and considering the needs of all parties. Nutrition experts provide nutritional guidance, exercise specialists offer exercise interventions, community hospitals conduct health examinations, family doctors ensure participant safety, senior living communities are responsible for promotion and publicity, and the elderly themselves contribute their suggestions and feedback. Fourthly, to ensure the reliability of the study, we will implement a comprehensive set of quality control measures, encompassing participant activity diaries, satisfaction surveys, online check-ins, lecture logs, and additional measures.

However, this study also has several potential limitations. Firstly, this study employs a single-blind design, as the nature of the interventions precludes blinding the staff administering the interventions or the participants themselves. Participants will be instructed not to disclose their intervention status to the assessors. However, this does not affect the progress or credibility of the project, as it reflects the participants’ true circumstances. Secondly, our conclusions regarding rural areas are conservative and cautious. Our model may not be directly applicable to rural settings, and the generalizability of our results should be approached with care. In the future, we plan to further explore this research in rural areas to gain more insights.

## Figures and Tables

**Figure 1 nutrients-17-03213-f001:**
[figure not shown]
Study flowchart inclusion to follow-up.

**Figure 2 nutrients-17-03213-f002:**
[figure not shown]
Detailed overview of the study.

**Figure 3 nutrients-17-03213-f003:**
[figure not shown]
Training wheel chart.

**Table 1 nutrients-17-03213-t001:** Description of the intervention content for each group.

Group	Intervention Components	Personnel	Frequency
Control Group	1. Routine community health lectures - Health education lectures - Provision of health education materials - Health counseling services	Trained project staff	Monthly
Multifaceted Nutrition Intervention	1. Daily dietary guidance - Provision of anti-inflammatory diet recipes, cooking tips, and a guidebook - Daily provision of 10 g of whey protein powder and 50 g of whole grains	Trained nutrition specialists	Weekly
	2. Personalized nutritional consultations - Integration of fixed-time, in-person hospital consultations with on-demand online consultations	Intelligent app/programs	At any time
	3. Health education - Lectures on chronic diseases, malnutrition, and frailty	Trained nutrition specialists	Every two weeks
Multifaceted Nutrition and Exercise Combined Intervention	Includes all components from the Multifaceted Nutrition Intervention group, PLUS: 4. Exercise guidance - Provision of an exercise intervention manual and wheel chart - Distribution of elastic resistance bands for resistance exercises	Trained sports specialists	Weekly

**Table 2 nutrients-17-03213-t002:** Outline of the health education activities for the elderly.

**No.**	**Activities**	**Content (Lecture Theme)**
The first month		
1	Lecture 1	Nutritional Status and Common Health Issues in the Elderly
2	Lecture 2	Unlocking the Health Code: Understanding Nutrients
Qualitative interviews: satisfaction survey and feedback		
The second month		
3	Lecture 3	Unlocking the Health Code: Recognizing the Nutritional Value of Foods
4	Lecture 4	Focus on Nutritional Screening: How the Elderly Can Identify Malnutrition
Qualitative interviews: satisfaction survey and feedback		
The third month		
5	Lecture 5	How the Elderly Should Plan Their Three Meals a Day
6	Lecture 6	To Live Longer, Overcome ‘Physical Frailty’—A New Perspective on Elderly Health Management
Qualitative interviews: satisfaction survey and feedback		
The fourth month		
7	Lecture 7	A Healthy Life, ‘Muscle’ is Essential—Nutritional Management of Sarcopenia
8	Lecture 8	Scientific Diet: Helping You ‘Keep Your Memory’
Qualitative interviews: satisfaction survey and feedback		

**Table 3 nutrients-17-03213-t003:** Schedule of assessments and outcome measures.

Measurements	Time Points				Instrument/Method of Assessment	Outcome Variables
	Baseline	3 Months	6 Months	12 Months		
Physical examination						
Height	Yes	Yes	Yes	Yes	Stadiometer	BMI
Weight	Yes	Yes	Yes	Yes	Lever scale	
Waist/Calf circumference	Yes	Yes	Yes	Yes	Tape	Waist/Calf circumference
Sebum	Yes	Yes	Yes	Yes	Sebaceous pliers	Body fat percentage
Body composition analysis	Yes	Yes	Yes	Yes	Body composition analyzer/bioelectrical impedance analysis technique	Body fat mass, body fat percentage, defatted body weight, muscle mass, body water, protein, inorganic salts, and other data
(Strength of one’s) Grip	Yes	Yes	Yes	Yes	Grip strength meter/adjust for palm size, measure with index finger second joint at a right angle, maximum effort	Grip strength measurements
Simple Physical Performance Based Assessment (SPPB)						
Balance testing	Yes	Yes	Yes	Yes	Timekeeping device/includes balancing in 3 different difficulty positions: feet together, half tandem standing, and tandem standing.	Test scores
3 or 4 meter pace test	Yes	Yes	Yes	Yes	Timekeeping device/walk at maximum speed. Record the shortest of two trials.	Test scores
Timed Sit-Stand Test	Yes	Yes	Yes	Yes	Timekeeping device/assess lower limb strength in elders by timing 5 rapid sit-to-stand cycles with a stopwatch.	Test scores
Frailty status						
Fried Frailty Phenotype	Yes	Yes	Yes	Yes	Scale questionnaire	Scale score
Tilburg Frailty Indicator	Yes	Yes	Yes	Yes	Scale questionnaire	Scale score
Frailty trajectories	Yes	Yes	Yes	Yes	Changes in frailty trajectories before and after the intervention, as measured by the Frailty Index	
Frailty recovery rates	Yes	Yes	Yes	Yes	Difference in frailty scores before and after intervention	
Nutritional status						
Malnutrition risk assessment	Yes	Yes	Yes	Yes	Scale questionnaire	Scale score
Nutritional literacy assessment for the elderly	Yes	Yes	Yes	Yes	Scale questionnaire	Scale score
Metabolomics						
Serum protein	Yes	Yes		Yes	Physiological and biochemical tests	Serum total protein, albumin, and transferrin
Urine 8-hydroxyguanosine (8-oxo-Gsn)	Yes	Yes		Yes	Physiological and biochemical tests	
Serum inflammatory factors	Yes	Yes		Yes	Physiological and biochemical tests	
Changes in serum differential metabolites	Yes	Yes			Utilize nontargeted metabolomics to assess serum metabolite changes pre- and post-intervention, elucidating the intervention’s mechanism	
Microbiota						
Changes in gut microbiota	Yes	Yes			Using the 16S sequencing method to detect changes in gut microbiota and differential bacterial genera among groups	
Comprehensive geriatric assessment						
Comprehensive geriatric assessment	Yes	Yes	Yes	Yes	Comprehensive Geriatric Assessment Questionnaire (CGAQ)	Physical assessment, functional assessment, medication review, social functioning assessment, environmental assessment, etc.
Intrinsic capacity						
Intrinsic capacity	Yes	Yes	Yes	Yes	Scale questionnaire	5-dimensional structure
State of health						
EuroQol Five Dimensions Questionnaire	Yes	Yes	Yes	Yes	EuroQol Five Dimensions Questionnaire	Mobility, self-care, usual activities, pain/discomfort, and anxiety/depression
Sleep conditions						
Pittsburgh Sleep Quality Index	Yes	Yes	Yes	Yes	Pittsburgh Sleep Quality Index	Rate the quality of sleep in the last 1 month
Participants’ satisfaction						
Participants’ satisfaction	Yes	Yes			Scale questionnaire	
Cognition function						
Cognition function	Yes	Yes	Yes	Yes	Mini-Mental State Examination (MMSE)	
Adverse event						
Adverse event	Yes	Yes	Yes	Yes		Serious, unexpected, and supervised adverse events

